# “Everybody Brush!”: Protocol for a Parallel-Group Randomized Controlled Trial of a Family-Focused Primary Prevention Program With Distribution of Oral Hygiene Products and Education to Increase Frequency of Toothbrushing

**DOI:** 10.2196/resprot.4485

**Published:** 2015-05-22

**Keywords:** oral hygiene, toothbrushing, dental devices, home care, dental care, communication, social support

## Abstract

**Background:**

Twice daily toothbrushing with fluoridated toothpaste is the most widely advocated preventive strategy for dental caries (tooth decay) and is recommended by professional dental associations. Not all parents, children, or adolescents follow this recommendation. This protocol describes the methods for the implementation and evaluation of a quality improvement health promotion program.

**Objective:**

The objective of the study is to show a theory-informed, evidence-based program to improve twice daily toothbrushing and oral health-related quality of life that may reduce dental caries, dental treatment need, and costs.

**Methods:**

The design is a parallel-group, pragmatic randomized controlled trial. Families of Medicaid-insured children and adolescents within a large dental care organization in central Oregon will participate in the trial (n=21,743). Families will be assigned to one of three groups: a test intervention, an active control, or a passive control condition. The intervention aims to address barriers and support for twice-daily toothbrushing. Families in the test condition will receive toothpaste and toothbrushes by mail for all family members every three months. In addition, they will receive education and social support to encourage toothbrushing via postcards, recorded telephone messages, and an optional participant-initiated telephone helpline. Families in the active control condition will receive the kit of supplies by mail, but no additional instructional information or telephone support. Families assigned to the passive control will be on a waiting list. The primary outcomes are restorative dental care received and, only for children younger than 36 months old at baseline, the frequency of twice-daily toothbrushing. Data will be collected through dental claims records and, for children younger than 36 months old at baseline, parent interviews and clinical exams.

**Results:**

Enrollment of participants and baseline interviews have been completed. Final results are expected in early summer, 2017.

**Conclusions:**

If proven effective, this simple intervention can be sustained by the dental care organization and replicated by other organizations and government.

**Trial Registration:**

Trial Registration: ClinicalTrials.gov NCT02327507; http://clinicaltrials.gov/ct2/show/NCT02327507 (Archived by WebCite at http://www.webcitation.org/6YCIxJSor).

## Introduction

### The Importance of Brushing Teeth Twice a Day

Dental caries is a disease with marked socioeconomic and regional disparities. In Oregon, untreated tooth decay is twice as common in low-income children than in children from higher income families (25% vs 13%) [1]. Similarly, almost three-quarters (73%) of 6 to 9 year old children in rural Central Oregon experience tooth decay, while the statewide average is 52% [1]. Dental caries can be prevented through regular toothbrushing with fluoridated toothpaste [2-5]. The American Academy of Pediatric Dentistry and the American Dental Association recommend that toothbrushing should be performed twice daily with a fluoride toothpaste and a soft toothbrush initially by the parent, and eventually by the child [6,7]. Relatively few parents and children fully follow this recommendation [8].

Successful behavioral interventions focus on helping people acquire skills and motivation to change behavior; they are sustained and comprehensive; and, they engage peers and family members to help maintain motivation [9]. Toothbrushing beginning in infancy is a good candidate behavior. It is similar to other mildly intrusive caregiving behaviors that parents accept learning, and infants grow to tolerate. Parents’ confidence to carry out this behavior is the best predictor of being caries free at age 4 [10,11]. Once established, childhood toothbrushing habits persist [12,13], but need to be reinforced.

Toothbrushing promotion programs that provide advice, free toothpaste, and toothbrushes at a child health visit and/or by mail have shown positive effects on parents’ behaviors, including the frequency of twice daily toothbrushing of their children [14]. When accompanied by social support and in-person instruction, toothbrushing promotion programs show decreases in childhood caries and improved oral hygiene [15-17]. A program similar to that designed for the intervention study described here led to increased frequency of toothbrushing at home [17], and a 30% reduction in tooth decay [16].

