### Eligibility and Recruitment

#### Selection of Participants

The study population will be approximately 20,000 families who are residents of the three county study setting, whose children/members are enrolled in the Oregon Health Plan and served by a single dental care organization. Inclusion criteria will be: (1) children less than 21 years old; (2) enrollment in the public health insurance program, Oregon Health Plan (Medicaid), and served by a single dental care organization, Advantage Dental Services, LLC; and (3) children whose home address is located in the three selected counties.

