#### Recruitment

Participants will be identified through an electronic search of the enrollment database of Advantage Dental Services. All Advantage Dental Services members meeting the eligibility criteria will be included. The intervention will be delivered to all children less than 21 years old, but the evaluation of parent-reported twice daily toothbrushing and dental caries outcomes will focus on children less than 36 months old. Advantage Dental Services decided to focus on these children because of the Healthy People 2020 objective OH-1.1 to, "Reduce the proportion of children age 3 to 5 years with dental caries experience", the belief in the lifelong benefit of establishing toothbrushing habits in early childhood, and the cost implications of providing care for children this age who experience tooth decay. Because of all this, a random subsample of parents/caregivers of children less than 36 months old and a random subsample of children less than 36 months old will be recruited. Parents/caregivers of children less than 36 months old to be interviewed will be recruited through telephone calls. Children less than 36 months old to be clinically examined will be recruited at community settings such as Head Start and the Special Supplemental Nutrition Program for Women, Infants, and Children. The parents/caregivers will have the quality improvement project explained to them and have the opportunity to opt out of the evaluation.

The University of Washington Institutional Review Board reviewed this study. Consistent with US Federal regulations, participants of this quality improvement project do not meet the criteria to be considered research subjects. University of Washington personnel will have access only to deidentified data.

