### Study Measures and Data Collection

#### Outcomes

The primary outcome for all children less than 21 years old will be restorative dental care received as a proxy for the presence of dental caries. Additionally, for children less than 36 months old at baseline, the other primary outcome will be parent/caregiver reported frequency of twice daily toothbrushing the child’s teeth. Secondary and tertiary outcomes will be cost of dental care for all participants; and, only for children less than 36 months old at baseline, parent/caregiver-reported oral-health related quality of life of the child, satisfaction with the program, and dental caries (tooth decay).

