#### Statistical Analysis Plan

Descriptive statistics (means, SD, counts, and percentages) will be calculated for all variables of interest overall and stratified by age group. Difference in difference models will be used to evaluate changes in frequencies and rates for pre versus post intervention effects within the intervention groups and for passive control versus active control versus test effects. Linear regression will be used to evaluate continuous outcomes and logistic regression will be used to evaluate binary outcomes. The primary hypothesis for all participants is that the test intervention group will have a lower number of restorative dental care procedures received than the active control group during the 18 months post intervention start date. For children less than 36 months old, the primary hypothesis is that the test intervention will increase toothbrushing frequency more than the active control intervention and no change in passive control group will be observed 10 months post intervention start date. Secondary hypotheses are that member satisfaction and oral health-related quality of life of the participants will be greater and that dental care costs and dental caries will be lower in the test intervention and active control than in the passive control.

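### The restorative-care count starts on the intervention start date, so treatment of existing decay dilutes the test versus active control contrast; a supporting count without the first 6 months should be pre-specified

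*Protocol article*

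**What the plan says.** The Statistical Analysis Plan section of the protocol article sets the primary hypothesis for all participants: the test group will have a "lower number of restorative dental care procedures received than the active control group", counted "during the 18 months post intervention start date". The Outcomes section defines the measure as "restorative dental care received as a proxy for the presence of dental caries".

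Eligibility covers "children less than 21 years old" who are insured through the plan and live in the three counties. Under Recruitment, "All Advantage Dental Services members meeting the eligibility criteria will be included". Being free of decay is not a criterion. No lag, washout or restriction to new lesions is attached to the count.

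On the background burden, the Introduction says "untreated tooth decay is twice as common in low-income children than in children from higher income families (25% vs 13" percent. That figure describes low-income children in Oregon, not the enrolled cohort.

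On timing, the Results section has the program delivered from August 2014 through April 2015, claims extracted in August 2015, and clinical examinations in July 2016. The Abstract adds: "Final results are expected in early summer, 2017".

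**The concern.** A restoration in the first weeks after the first kit almost certainly treats decay that was already there. New decay has to form, be found at a visit and be treated before it can appear in claims. The two arms compared here also receive the same kits. They differ only in the postcards, calls and advice line, which are delivered over 9 months, so half of the 18-month window passes while the contrast is still being delivered.

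The early months thus add similar counts to both arms, with noise and little signal. The difference-in-difference model does not remove this: it subtracts claims from before the start, not old decay treated after it.

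The stake is practical. The Discussion says the evaluation will show whether the intensive instruction and support could be dropped. A diluted result would favour dropping them.

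**Working it through.** **The plan's own figure.** There is none for this outcome. The Sample Size section says no calculation was done and about 20,000 participants was judged enough. Its stated sizes (39, 66, 206 and 113 per group) reproduce with a two-sided alpha of .025 and pooled variance, but belong to brushing and caries.

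**Check 1: dilution by a backlog.** Let b be the share of children whose existing decay is treated in the window, and i the risk of a restoration for new decay. With a 30% reduction in new decay (the Introduction's figure for a similar program):

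- control: pc = b + (1 − b)i
- test: pt = b + (1 − b)i × 0.70
- observed relative reduction: 1 − pt/pc

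Taking 25% with untreated decay, half treated gives b = 0.125 and all treated gives b = 0.25. The treated share and i are assumptions.

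| i | b = 0.125 | b = 0.25 |
|---|---|---|
| 5% | 7.8% | 3.9% |
| 10% | 12.4% | 6.9% |
| 20% | 17.5% | 11.3% |
| 30% | 20.3% | 14.2% |

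Example: i = 10%, b = 0.125 gives pc = 0.2125, pt = 0.18625 and a reduction of 12.4%. With 10,797 per arm and a two-sided alpha of .05 (assumed, clustering ignored), power is about 94% or higher for i of 10% or more. At i = 5% it is 74% (b = 0.125) or 45% (b = 0.25).

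**Check 2: dilution by a lag.** Assume a constant procedure rate and a lag L before the program affects procedures. The preventable share of months 0–18 is (18 − L)/18. For L = 6, 9 and 12 a 30% reduction shows as 20%, 15% and 10%. Over months 7–18 the share is (18 − L)/12, and the same reduction shows as 30%, 22.5% and 15%.

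**Check 3: what excluding 6 months does to power.** Assume one value per family, mean 1.0 and SD 2.5 over 18 months, a true 15% reduction in new decay, 10,797 per arm, two-sided alpha .05, and variance proportional to window length.

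- SE, months 0–18 or 7–24: 2.5 × √(2/10,797) = .0340
- SE, months 7–18: .0340 × √(12/18) = .0278
- absolute difference, months 0–18 and 7–18 alike: .15 × (18 − L)/18 = .100, .075, .050
- absolute difference, months 7–24: .15 × (24 − L)/18 = .150, .125, .100, if the effect persists in full

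Power = Φ(difference/SE − 1.96).

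| Window | L = 6 | L = 9 | L = 12 |
|---|---|---|---|
| 0–18 | 84% | 60% | 31% |
| 7–18 | 95% | 77% | 44% |
| 7–24, full persistence | 99% | 96% | 84% |

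**Check 4: no persistence.** If only decay formed during the 9 months of delivery is prevented, the affected procedures fall in months 7–15, 10–18 and 13–21 for L = 6, 9 and 12. Months 0–18 and 7–18 each contain 9, 9 and 6 of these months; months 7–24 contains 9 in each case. The differences are .15 × 9/18 = .075 or .15 × 6/18 = .050.

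| Window | L = 6 | L = 9 | L = 12 |
|---|---|---|---|
| 0–18 | 60% | 60% | 31% |
| 7–18 | 77% | 77% | 44% |
| 7–24, no persistence | 60% | 60% | 60% |

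Dropping the first 6 months helps in every column. Adding months 19–24 helps only at L = 12 and costs power at L = 6 and 9.

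**Check 5: extraction date.** August 2014 to August 2015 is about 12 months, so an 18-month count cannot be complete. At 12 months the preventable share is (12 − L)/12 = 50%, 25% or 0%.

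**The case against.** The strongest case against is that all restorative care from program start is a legitimate outcome for a pragmatic trial run by a payer that wants to move resources away from restorations. That stands, and is why the primary count should not be replaced.

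An additive backlog also leaves the expected absolute difference in counts unchanged; it shrinks the relative reduction and adds variance. That stands too. The benefit of excluding early months is less noise, not more signal.

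A reader might infer that moving the window to months 7–24 is worth a sample about 2.3 to 4 times as large (squared ratios of preventable shares: 2.25, 2.78 and 4.0). The documents do not support this. Months 0–24 hold the same absolute effect as months 7–24, so that gain in signal comes from adding months 19–24. It also assumes the full effect persists after delivery ends in April 2015, whereas the Introduction says brushing habits persist but need reinforcement. Check 4 shows the gain can vanish.

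A reader might also infer that the trial is underpowered. With a 30% effect and the inputs of Check 3, months 0–18 already give about 100%, 99% and 84%. The two-sample test is also not the planned difference-in-difference analysis.

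**Conclusion.** The concern holds as one of lost sensitivity. Counting from the start date, in children not required to be decay-free, includes treatment that the program could not have prevented. Both arms carry this backlog equally by randomization, so there is no bias between them.

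The size cannot be fixed from the documents. The 25% figure is for low-income children across Oregon, while this cohort runs from infancy to age 20; the share treated within the window, the lag, the mean and the SD are all assumed. Over the ranges shown, a 30% effect on new decay appears as roughly 4% to 20%. Power may remain adequate if the effect is near 30% and new restorations are common. It is more exposed if the messages add a smaller effect to identical kits.

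For any lag of 6 months or more, excluding the first 6 months keeps the same absolute signal with less noise. For a shorter lag some signal is lost. At L = 3, Check 3 gives z = .125/.0340 = 3.7 for months 0–18 against .100/.0278 = 3.6 for months 7–18, which is close to even. At L = 0 it gives .150/.0340 = 4.4 against 3.6. That is a further reason to make this analysis supporting rather than primary.

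Separately, the August 2015 extraction contradicts the 18-month window.

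**What to change.** - Keep all restorative care from the start date as the primary count.
- In the Statistical Analysis Plan section, pre-specify a key supporting test versus active control analysis that excludes procedures in the first 6 months. Fix it before any claims are extracted.
- Reconcile the August 2015 extraction with the 18-month window.
- When the extraction is moved, consider taking claims to month 24, alongside the July 2016 examinations and still ahead of results in 2017, so that the supporting window can run over months 7–24. State that any gain from months 19–24 depends on the effect persisting after April 2015.

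The cost is a little more analysis, a later extraction and somewhat more loss of coverage by month 24. The power figures above do not allow for that loss.

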### Aims and Objectives

Our aim is to design, deliver, and evaluate the “Everybody Brush!” program, a quality improvement effort of Advantage Dental Services, LLC for children and adolescents enrolled in Medicaid and their families in Central Oregon. Our primary objective is to determine if the intervention is effective in reducing restorative dental care treatment and increasing the percentage of parents who report twice daily toothbrushing of their child’s teeth. This objective reflects key evidence-based recommendations of brushing teeth with fluoride toothpaste (evidence level I) twice a day (evidence level IV). Our secondary objectives are to investigate if the intervention is effective in improving oral health and oral-health related quality of life and reducing dental care costs.

This protocol follows the SPIRIT [18] and Consolidated Standards of Reporting Trials (CONSORT) statements [19] and relevant extensions [20]. The main research question is, “Does the distribution of free toothpaste and toothbrushes with behavioral psychosocial health messages and telephone support, compared with distribution of free toothpaste and toothbrushes alone or no intervention, improve home toothbrushing behavior and reduce the restorative care of children of low-income families?”.

## Methods

### Design, Setting, and Selection of Participants

The study design is a parallel-group randomized controlled trial. The setting is three counties in rural Central Oregon (Crook, Deschutes, Jefferson).

### Eligibility and Recruitment

#### Selection of Participants

The study population will be approximately 20,000 families who are residents of the three county study setting, whose children/members are enrolled in the Oregon Health Plan and served by a single dental care organization. Inclusion criteria will be: (1) children less than 21 years old; (2) enrollment in the public health insurance program, Oregon Health Plan (Medicaid), and served by a single dental care organization, Advantage Dental Services, LLC; and (3) children whose home address is located in the three selected counties.

#### Recruitment

Participants will be identified through an electronic search of the enrollment database of Advantage Dental Services. All Advantage Dental Services members meeting the eligibility criteria will be included. The intervention will be delivered to all children less than 21 years old, but the evaluation of parent-reported twice daily toothbrushing and dental caries outcomes will focus on children less than 36 months old. Advantage Dental Services decided to focus on these children because of the Healthy People 2020 objective OH-1.1 to, "Reduce the proportion of children age 3 to 5 years with dental caries experience", the belief in the lifelong benefit of establishing toothbrushing habits in early childhood, and the cost implications of providing care for children this age who experience tooth decay. Because of all this, a random subsample of parents/caregivers of children less than 36 months old and a random subsample of children less than 36 months old will be recruited. Parents/caregivers of children less than 36 months old to be interviewed will be recruited through telephone calls. Children less than 36 months old to be clinically examined will be recruited at community settings such as Head Start and the Special Supplemental Nutrition Program for Women, Infants, and Children. The parents/caregivers will have the quality improvement project explained to them and have the opportunity to opt out of the evaluation.

The University of Washington Institutional Review Board reviewed this study. Consistent with US Federal regulations, participants of this quality improvement project do not meet the criteria to be considered research subjects. University of Washington personnel will have access only to deidentified data.

### Randomization and Blinding

Families will be randomized with equal probability to one of three study conditions using computer-generated random numbers. A biostatistician at the University of Washington using a dataset containing only family identification codes and without personal identifying information will generate the allocation schedule for random assignment. The treatment allocation for each participant will be kept in Seattle, and the biostatistician will reveal the treatment allocation to local investigators when they are ready to implement the program. Personnel involved in the delivery of the intervention and trial participants will not be blinded to group allocation. Interviewers will be blinded to group allocation.

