### Passive Control Condition

Participants will receive the usual Advantage Dental Services practices, which may include receiving information about dental benefits via telephone and mail. This group will be on a waiting list for the trial intervention for 9 months and will then receive one toothbrushing kit. Only children less than 36 months old and their families will be included in this control condition.

By the conclusion of the study, all families will have received toothbrushing supplies. This principle, that all eligible Advantage Dental Services members will have the opportunity to benefit, is part of the organization’s mission.

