### Trial Status

Participants were selected (N=21,743 families, 2857 with children less than 36 months old at baseline) and randomly assigned to the test (n=10,797), active control (n=10,796), and passive control (n=150 families with children less than 36 months old) conditions. A random sample of parents/caregivers of children less than 36 months old was interviewed (n=450, 150 for each test, active, and passive control conditions). The program has been deployed.

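### Passive control is not an equal-probability arm: it is 150 families, all with a child under 36 months, so the cost comparison with it, as written for all participants, is not protected by randomization

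*Protocol article*

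**What the plan says.** Randomization and Blinding gives the allocation rule: "Families will be randomized with equal probability to one of three study conditions".

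Two other sections describe something different. Passive Control Condition restricts that arm: "Only children less than 36 months old and their families will be included in this control condition". Trial Status gives the total, "Participants were selected (N=21,743 families, 2857 with children less than 36 months old at baseline", and the arm sizes: "randomly assigned to the test (n=10,797), active control (n=10,796", and "passive control (n=150 families with children less than 36 months old) conditions".

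On cost, the Outcomes section says: "Secondary and tertiary outcomes will be cost of dental care for all participants". The same sentence limits quality of life, satisfaction and caries to children under 36 months at baseline, but not cost. The Statistical Analysis Plan section then hypothesises that "dental care costs and dental caries will be lower in the test intervention and active control than in the passive control", and attaches no age restriction to cost. It plans difference-in-difference models across the three conditions. Age stratification is mentioned only for descriptive statistics, and the confounders named for all participants (parent's age, family size, race/ethnicity) do not include the child's age.

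**The concern.** Randomization protects a comparison only among families that could have been assigned to either side of it. If the passive arm could take only families with a very young child, most test and active control families have no randomized passive counterpart. An all-participant cost contrast then compares families of toddlers with families whose children may be as old as 20, and an age difference can be read as an effect of the programme.

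The allocation statement also matters in itself. A reader who trusts it would take the passive arm for a random third of the whole population and would carry any finding against no intervention over to all ages. The Discussion says that the evaluation will inform whether the programme is sustained and expanded.

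**Working it through.** **Inputs** (Trial Status): N = 21,743 families; 2,857 with a child under 36 months, read here as a count of families; arms 10,797, 10,796 and 150, with all 150 passive families having such a child.

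**1. Do the counts fit equal probability?**
- Sum of arms: 10,797 + 10,796 + 150 = 21,743, so the counts are internally complete.
- Expected per arm: 21,743 / 3 = 7,247.7. SD = √(21,743 × 1/3 × 2/3) = 69.5. The passive arm lies (150 − 7,247.7) / 69.5 ≈ −102 SD away.
- If equal probability applied only to families with a child under 36 months: 2,857 / 3 = 952.3, SD = 25.2, and (150 − 952.3) / 25.2 ≈ −32.
- Neither reading gives 150. The counts do fit another scheme: 150 families set aside for passive control and the other 21,593 split 1:1 (21,593 / 2 = 10,796.5).

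**2. Who could enter passive control?**
- Families without a child under 36 months: 21,743 − 2,857 = 18,886, of which 0 are in passive control.
- Families with one: 150 / 2,857 = 5.3% are in passive control.

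**3. Age mix of the arms**
- Passive: 150 / 150 = 100% have a child under 36 months.
- Test plus active: (2,857 − 150) / 21,593 = 2,707 / 21,593 = 12.5%. The other 18,886 / 21,593 = 87.5% have no passive counterpart.

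**4. What the difference-in-difference model leaves**

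Let the mean pre-to-post change in cost, with no intervention effect, be Y in families with a child under 36 months and O in the others, weighting families equally and taking Y to be the same in all arms.
- Change in test plus active: 0.125 × Y + 0.875 × O.
- Change in passive: Y.
- Difference in differences: 0.875 × (O − Y).

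A constant cost-level gap drops out. Seven eighths of any difference in trend stays in. The document gives no costs by age, so neither the size nor the sign of O − Y is known.

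**5. What a restricted contrast could detect**

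Minimum detectable difference in SD units, 80% power, ignoring clustering and skewed costs: (z for alpha + 0.842) × √(1/n1 + 1/n2).
- 150 versus about 1,353 per arm (2,707 / 2, assuming an even split): 2.80 × 0.0861 = 0.24 SD at two-sided alpha 0.05; 3.08 × 0.0861 = 0.27 SD at 0.025.
- 150 versus 150 (interviewed families only): 2.80 × 0.1155 = 0.32 SD at 0.05; 3.08 × 0.1155 = 0.36 SD at 0.025.

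**The case against.** **The cost hypothesis may already mean the young stratum.** It sits in one sentence with satisfaction, quality of life and caries, which are limited to children under 36 months, and the passive arm holds only such families. A same-age contrast is a plausible intention, and an analysis set could be defined in a document that is not shown. This stands in part: the text does not prove that a confounded analysis is planned. But Outcomes limits the other measures by age and expressly does not limit cost, so the plan as written allows the mixed contrast.

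**The planned model deals with age.** Difference in difference does remove stable gaps. It still needs parallel cost trends between families with toddlers and families with older children, and this allocation does not supply that.

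**Passive families can include older siblings.** The section on the kit puts the average family at 3 or 4 children, so the age imbalance is not total at child level. Families without a young child are still absent.

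**Stronger readings that the documents do not support:**
- *The programme will look costlier by a calculable amount.* If families without a young child cost 1.5, 2 or 3 times as much (an assumption), crude cost ratios against passive control would be 1.44, 1.87 or 2.75. These are level comparisons, not the planned model. No source in the document supports ratios above 1, and the Discussion stresses high costs in young children with rampant caries.
- *The main research question demands a comparison with no intervention in older children.* It does include the words "compared with distribution of free toothpaste and toothbrushes alone or no intervention", but refers broadly to children of low-income families. The formal restorative hypothesis is test versus active control.
- *Restriction by age makes the contrast unbiased.* That holds only if the 150 were a random draw from the 2,857. All 150 passive families were interviewed, against 300 / 2,707 = 11% of the others. If the 150 came out of the interview sample, they differ from the remaining families by having been reached and not having opted out. If they were drawn at random first, the unequal interview fraction causes no bias by itself.

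**Conclusion.** The contradiction over allocation is certain: 150 of 21,743 families (0.7%), all from one age stratum, is not equal probability. The cost point holds with less certainty, because it rests on reading the hypothesis without an age limit, as it is written. On that reading, an arm with 100% under-36-month families is set against arms with about 12.5%. The contrast then depends on parallel age-related cost trends and not on randomization, and the remaining bias has unknown size and sign.

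A reader might infer that the trial's main results are compromised. They are not. Restorative care is tested between test and active control, which are split 10,797 to 10,796, and the toothbrushing hypothesis is already confined to children under 36 months. What is affected is the description of the randomization, the passive-control cost hypothesis, and any all-ages conclusion against no intervention.

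**What to change.** 1. Replace the equal-probability statement with the allocation actually used, including how and when the 150 passive families were drawn, and whether this was before or after selection for interview.
2. State that the passive-control cost contrast, and any other passive-control contrast from claims, is confined to families or children in the under-36-month stratum.
3. If the 150 were drawn from the interview sample, make the 450 interviewed families the comparison set. Otherwise use them for a sensitivity analysis.
4. Limit all-ages conclusions on restorative care and cost to test versus active control, that is, to messages and telephone support added to kits.

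The cost is protocol wording and one analysis-set definition. The article describes the claims extraction as still to come, so both can be settled before it. The price is precision: the passive cost contrast becomes 150 families versus about 1,353 per arm (assuming an even split), or 150 versus 150 if only interviewed families can be used.
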